### Recruitment procedures and group allocation

Daily, medical charts of all new stroke new admissions with a diagnosis of stroke and emergency room visits to any of the six targeted sites are reviewed by site-designated nurses to identify individuals with a potential first mild stroke. Once eligibility is ascertained, she explains the research to interested individuals and gives them a hard copy of the information and consent form thus giving time to potential participants to read more about the trial and think it over before providing consent. Informed consent is obtained upon the first phone contact by the research staff. If participants do have another stroke in the first month post-stroke, before baseline measures are collected and become ineligible, they are excluded. The site-designated nurse is also asked to document comorbidities based on information available in the medical chart. To ensure comparability between the two groups and using the information collected from the baseline measures, participants are being stratified according to the presence of important comorbidity (score ≥ 4 on the Comorbidity Index [37]) versus not (score < 4 on the Comorbidity Index [37]) and randomly allocated (ratio one-to-one) either to the WE CALL or YOU CALL group. A stratified block randomization procedure is done using a random-number generator on a computer and blocks of four. Randomization is carried out by a person who is not involved in the research [39]. Inclusion and exclusion criteria can be found in Figure 2.

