## Methods/Design

### Design

We are conducting a randomized clinical trial, over the first six months post-stroke, with a follow-up at one year (see figure 1). Multi-site recruitment across three Canadian provinces, Québec (Montréal), Ontario (Brantford, Chatham and Kitchener-Waterloo) and Alberta (Calgary), allows a representative sample of participants exposed to different levels of services post stroke such as differing access to Secondary Stroke Prevention Clinics. The target population for this study is all individuals/adults who sustained a first "mild" stroke and who are discharged home within three weeks of being admitted to an acute care hospital. Daily chart reviews of all new stroke admissions are being performed by a site-designated-research-nurse (who is not the treating clinician) to identify potential first mild stroke patients. Potential participants are then approached for further screening. Eligible and interested patients are requested to provide informed consent, and receive a copy of the consent form. Participants are being assessed at baseline (quality of life, participation and depression) in the first month post-stroke by way of a telephone interview. Phone interviews were shown to be as reliable as face-to-face interviews when measuring variables as complex as functional status [36]. They are then being allocated randomly, using stratified block randomization, to one of two groups: 1) "WE CALL" or 2) "YOU CALL". Stratification is done according to level of comorbidity (no or low comorbidity versus high as indicated by a score ≥ 4 on the Comorbidity Index [37]) as this variable is important to the primary outcomes: unplanned-use of health services for negative events and quality of life. Furthermore, to consider the potential effect on outcomes of availability of secondary prevention clinic and urban versus rural areas, parallel randomization (separate randomization) occurs for each province.

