**Figure 1 F1:**
[figure not shown]
**Study plan**. 1. Informed consent, baseline assessment (primary and secondary outcomes) and randomisation; 2. Three-month primary outcomes assessment time; 3. Post- intervention assessment time (primary & secondary outcomes); 4. Self- reported use of health services assessment (from month #6 to #9); 5. Follow- up assessment (primary & secondary outcomes).

The interventions are being delivered from Montreal (Québec) with close collaboration with a site-designated nurse for the identification of local community resources. Participants are blind to the underlying hypotheses being tested but cannot be blinded to the intervention. Outcome assessors are blind to group assignment.

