4. **Depression **is measured using the **Beck Depression Inventory II **(BDI-II) [62] created to correspond with the updated DSM-IV criteria for depression. It is composed of 21 items answered on a four-point Likert scale (score ranging 0 - 63) with a higher score indicating a greater severity of depression. A score of 0-13 is considered none or minimal range depression; 14-19 mild depression; 20-28 moderate depression; and 29-63 severe depression. Because of its relatively low reliance on somatic symptoms, the BDI is considered one of the more useful tools in assessing post-stroke depression [63]. It has strong psychometric properties: it has been shown to be responsive to change in 86 psychiatric patients treated with antidepressants [64] and was also as sensitive to change over time as DSM-IV criteria in a sample of 128 first-stroke followed for one year post-stroke [65]. A five-point difference is considered as a minimally important clinical difference [66].

Apart from the outcome measures indicated above, **sociodemographic data **(such as age, gender, living alone or not, socioeconomic status, etc.) are being collected at baseline. **Comorbidity **is also assessed at baseline by way of a medical chart review (by the site-designated nurse) using the Comorbidity Index [37] for stratification purposes. This index has been developed and validated for stroke outcomes research. It consists of a list of potential comorbidities rated on a four-point scale measuring how they impact on daily functioning: a score of four refers to major impact and it is therefore used as a threshold. All measures are available both in English and French.

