## Current study status

Enrolling participants in the six sites.

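### One fixed block size of four, published during enrolment, leaves an avoidable risk that recruiting nurses could anticipate some allocations

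*Protocol article*

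**What the plan says.** Under Recruitment procedures and group allocation, participants are "randomly allocated (ratio one-to-one) either to the WE CALL or YOU CALL group". The method follows: "A stratified block randomization procedure is done using a random-number generator on a computer and blocks of four". No other block size is mentioned. The same section adds: "Randomization is carried out by a person who is not involved in the research".

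The Design section sets the strata. For comorbidity: "Stratification is done according to level of comorbidity (no or low comorbidity versus high as indicated by a score ≥ 4 on the Comorbidity Index". For geography: "parallel randomization (separate randomization) occurs for each province". Three provinces by two comorbidity levels give six lists.

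The site-designated nurse has several tasks:
- She reviews charts, identifies eligible patients, explains the trial and hands over the consent form (Recruitment procedures and group allocation).
- She rates the stratifying factor: comorbidity "is also assessed at baseline by way of a medical chart review (by the site-designated nurse" (Detailed description of outcome measures).
- She has contact with the intervention team, which works from Montréal "with close collaboration with a site-designated nurse for the identification of local community resources" (text after Figure 1).

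That text also says that participants cannot be blinded to the intervention, while outcome assessors are blind. Consent is taken by research staff by telephone, and allocation follows the baseline telephone interview. Under Current study status the article reports: "Enrolling participants in the six sites".

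**The concern.** A constant block size lets anyone who knows it, and who knows the earlier allocations in a list, work out some of the next ones. Here the size is in print during recruitment. Three functions meet in one role: choosing whom to approach, scoring the stratum, and contact with the team that delivers the interventions. The Interventions section describes referral to local community services under WE CALL, so a request for local resources about a named participant would hint at that participant's arm.

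A nurse who could anticipate the next arm might, even unintentionally, be more or less active in approaching a given patient, or rate a borderline patient above or below the cut-off of 4. Blinding of assessors does not protect against this. Both primary outcomes are self-reported, and the main six-month comparison is an independent-samples t-test on change scores, which is not designed to correct for selective enrolment.

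**Working it through.** The article gives no figure for predictability, so there is none to reproduce. The inputs are 1:1 allocation, one block size of four, and 3 × 2 = 6 lists.

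**Upper bound and effect of delay.** A block holds two assignments per arm, and its 6 possible orders are equally likely. Suppose an observer knows where each block starts, knows each patient's place in the list, and always guesses the arm with more places left. The observer knows all earlier allocations in the list except the latest k. The probability of a correct guess at each position is:

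| Position in block | k = 0 | k = 1 | k = 2 | k = 3 |
|---|---|---|---|---|
| 1st | 1/2 | 1/2 | 1/2 | 1/2 |
| 2nd | 2/3 | 1/2 | 1/2 | 1/2 |
| 3rd | 2/3 | 2/3 | 1/2 | 1/2 |
| 4th | 1 | 2/3 | 2/3 | 1/2 |
| Sum / 4 | 2.833/4 = 70.8% | 2.333/4 = 58.3% | 2.167/4 = 54.2% | 2/4 = 50% |
| Certain | (1/3 + 1)/4 = 33.3% | (1/3)/4 = 8.3% | 0 | 0 |

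The entries of 2/3 arise in two ways:
- If only the first assignment is known, three places are left and two belong to the other arm: 2/3.
- If the first two are known, they are equal with probability 1/3 and the rest is certain. Otherwise the guess is even: 1/3 + (2/3)(1/2) = 2/3.

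**Shared lists.** Lists are provincial, and the Design section names three Ontario cities. A simulation used 64 participants per list (384/6, assuming equal lists). The observer saw a random part of the list and guessed from the imbalance seen so far. The correct-guess rate was about 54% with half the list visible and about 53% with one third visible, roughly the position of a nurse at one of three Ontario sites. In Alberta only Calgary is named, so one site appears to feed both lists there. That setting comes closest to the upper bound.

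**After a change of block size.** In the same simulation with the whole list visible, and with the observer guessing from the running imbalance, accuracy was about 69% for sizes 4 and 6 mixed at random, and about 68% for sizes 4, 6 and 8. Fixed blocks of four give 70.8%. The gain lies mainly in the certain assignments: an observer who does not know the sizes cannot tell when an arm is used up.

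**The case against.** A reader might infer that the nurse helps to deliver WE CALL, that requests for local resources show who is in that arm, and that upcoming assignments can therefore be predicted. The document does not support that chain:
- The nurse's collaboration is described for the interventions in general, and trained health care professionals deliver both. Identifying a community's resources needs no participant's name.
- Referral is described under WE CALL, but the YOU CALL professional must answer participants' questions fully, which could also involve local resources. WE CALL referral is itself made only when needed. Neither a request nor its absence would identify an arm with certainty.
- Nothing in the article tells the nurse any allocation. How allocations are communicated and concealed may be set out in the full protocol.
- When a patient is approached, telephone consent, the baseline interview and possible exclusion for a second stroke still lie ahead. The patient's place in the list is not yet known. Three recent allocations unknown in a list are enough to remove all predictability.
- Steering a patient by rescoring comorbidity would require knowing the state of both lists at a later randomization date.

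All of this stands, and it limits the size of the risk. It does not remove it. An outside randomizer hides the list but not what can be inferred from past allocations once the block size is known. Consent by other staff leaves the nurse's influence on who is approached and how comorbidity is scored. The one parameter that inference needs has been published without need.

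**Conclusion.** The point holds as an avoidable risk of prediction, not as demonstrated predictability, and no subversion of allocation is alleged. The figures of 33% certain and 71% guessed correctly are an upper bound. They assume an observer who knows every earlier allocation in a list, and the document neither grants nor rules out that knowledge. More realistic conditions give 58%, 54% or 50% with one, two or three recent allocations unknown, and about 53% to 54% with only part of a list visible (under the assumption of a random visible part). A reader might go on to infer that selection bias is present or likely. The article gives no basis for that. The case for acting is that the remedy is nearly free and that neither assessor blinding nor the planned comparison would repair selective enrolment.

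**What to change.** For participants still to be enrolled:
1. Keep recruiting nurses unaware of arms. Requests to them for local resources should carry neither participant identifiers nor allocation. This is the more important part, because it closes the possible route to past allocations.
2. Replace the fixed block of four with randomly varying sizes, for example 4, 6 and 8, within the same province and comorbidity strata, and do not disclose the sizes to sites. This mainly removes certain assignments. On its own it lowers best-guess accuracy only from 70.8% to about 68%.

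The cost is a new computer-generated list and a short procedural note. The largest imbalance within a list at the end of enrolment rises from 2 to 4 (half of a block of 8). If all six lists ended at that extreme in the same direction, the total would be 6 × 4 = 24, against 6 × 2 = 12 now, among 384 participants. Allocation ratio, strata and sample size do not change. If the full protocol already keeps nurses unaware of allocations, a sentence saying so settles the first part.

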**Figure 2 F2:**
[figure not shown]
**Eligibility criteria**.

### Primary and secondary outcome measures

The two primary outcomes are **unplanned-use of health services for negative events **and **quality of life**. Secondary outcomes include participation level, depressive symptoms and planned-use of health services for health promotion and secondary prevention. Unplanned use of health services for negative events is crucial to consider as a primary outcome as it reflects important health problems for individuals, is very costly to the individual and society and evidence suggests it can be decreased with adequate secondary prevention strategies. Quality of life is chosen as the other primary outcome, having emerged as *the ultimate outcome upon which the impact of stroke interventions and stroke programs should be evaluated *(Canadian Stroke Network). An economic evaluation comparing the two interventions will be also performed.

### Detailed description of outcome measures

1. **Unplanned-use of health services and planned-use **is being identified as the number of doctor visits, emergency or medical clinic visits, number of hospitalizations and any other use of other health care professionals (e.g. social worker, psychologist, physical therapist, occupational therapist, etc.) for the 6-month period of the study and an additional six months follow up period. To minimise recall bias, these data are being collected by way of a frequency calendar where each participant notes the health services they used, reasons (e.g. a fall, dizziness, stroke, follow up appointment, physical therapy, etc.) and most importantly if the visit was planned (scheduled) or not (emergency). At the time of data coding, each entry is being scrutinized by three stroke specialist health professionals, not involved in the study, to differentiate noise (such as emergency for a cold or planned-visits for foot care) versus any stroke-related use of the health care system (e.g. emergency for a fall, dizziness, or follow up visit for hypertension or any other risk factors) upon which the program aims to have an impact. Each entry is being dichotomised as either planned for health promotion/prevention or unplanned for a negative event. Using administrative data from each province was considered; however, given the high reliability between self-reported and administrative data of health-services use [40], we chose to rely on self-reported use only. Furthermore, this method of using a calendar has been successfully used with elderly individuals [40]. Given the high prevalence, especially in the early transition period following stroke onset, of stroke recurrence [41], medications errors [42,43]., of falls [44], depressive symptoms [45,46], etc., we estimate a mean number of unplanned-visit equal to three in the first six months post-stroke with a standard deviation of one.

2. A number of **quality of life **tools were reviewed (e.g. SF-36, Stroke Impact Scale, Quality of Life Index) and the tool chosen was a compromise between psychometric properties and adequacy of content for mild stroke. The 32 item questionnaire **Quality of Life Index **(QLI) [47] which was developed from Ferran's conceptual model of quality of life and which has been used with a stroke clientele [48] was chosen as the primary outcome. Each item of the QLI as relating to four life domains (health and functioning, socio-economic, psychological/spiritual and family), is evaluated in terms of satisfaction and importance on a six-point scale. Scores for each domain and a global score are expressed from 0-to-30, with a higher score indicating a better quality of life. These four life domains relate well with the main issues covered through the WE CALL intervention. Its has shown to have adequate psychometric properties (concurrent validity, test-retest reliability and high internal consistency: α = 0.90) [47] and thus should be responsive to therapy-induced change [49,50]. A one-point difference was observed in the first six months post-stroke descriptive follow-up (n = 63) for an effect size of 0.33 [51]. A two-point difference is considered a clinically meaningful change leading to a moderate effect size of 0.66. The **EQ-5D **which is composed of 5 items rated on a three-level scale [52] is also being completed as this questionnaire provides utility estimates needed to performed cost-utility analysis The EQ-5D is one of the recommended instruments by the Canadian Agency for Drugs and Technologies in Health (CADTH) [53].

3. The **LIFE-H **[54] is used to measure the **ICF participation domains **[55]. This questionnaire is composed of 77 items and covers 12 domains of participation [56]. The first six domains, Nutrition, Fitness, Personal care, Communication, Housing, and Mobility refer to the accomplishment of daily activities whereas the last six, Responsibilities, Relationships, Community life, Education, Employment and Recreation refer to the accomplishment of social roles. Participants are asked about the degree of difficulty in accomplishing the activity or the social role (without difficulty, with difficulty, by substitution or not realised) as well as assistance used (technical assistance, physical arrangements or human help). From their answers to these two simple questions, scores for each domain and a global score are derived and expressed from 0-to-9 where a higher score indicates better participation. It takes between 20-30 minutes to administer. The WE CALL intervention, through support and information about available community resources, is expected to foster improvements in many different domains of community reintegration covered by the LIFE-H, especially in regards to social roles. The LIFE-H has excellent psychometric properties [55,57], it has been extensively used in stroke [16,49,58-61] and is responsive to spontaneous recovery in individuals with "mild" stroke without showing ceiling effects [16]. An improvement of one-point out of a maximum score of nine is considered to be clinically important [55].

4. **Depression **is measured using the **Beck Depression Inventory II **(BDI-II) [62] created to correspond with the updated DSM-IV criteria for depression. It is composed of 21 items answered on a four-point Likert scale (score ranging 0 - 63) with a higher score indicating a greater severity of depression. A score of 0-13 is considered none or minimal range depression; 14-19 mild depression; 20-28 moderate depression; and 29-63 severe depression. Because of its relatively low reliance on somatic symptoms, the BDI is considered one of the more useful tools in assessing post-stroke depression [63]. It has strong psychometric properties: it has been shown to be responsive to change in 86 psychiatric patients treated with antidepressants [64] and was also as sensitive to change over time as DSM-IV criteria in a sample of 128 first-stroke followed for one year post-stroke [65]. A five-point difference is considered as a minimally important clinical difference [66].

Apart from the outcome measures indicated above, **sociodemographic data **(such as age, gender, living alone or not, socioeconomic status, etc.) are being collected at baseline. **Comorbidity **is also assessed at baseline by way of a medical chart review (by the site-designated nurse) using the Comorbidity Index [37] for stratification purposes. This index has been developed and validated for stroke outcomes research. It consists of a list of potential comorbidities rated on a four-point scale measuring how they impact on daily functioning: a score of four refers to major impact and it is therefore used as a threshold. All measures are available both in English and French.

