### The research objective

The purpose of this study is to assess the effectiveness, for individuals who experience a first "mild" stroke, of a sustainable, low cost, multimodal support intervention (comprising information, education and telephone support) - "***WE CALL***" compared to a passive intervention (providing the name and phone number of a resource person available if they feel the need to) - "***YOU CALL***", on two primary outcomes: unplanned-use of health services for negative events and quality of life. Secondary outcomes include participation level, depressive symptoms, and planned-use of health services for health promotion and secondary prevention. A secondary objective is to *explore *the contribution of potential explanatory variables such as age, gender, living alone versus with a significant other, comorbidity level and access (or not) to a secondary stroke prevention clinic, on outcomes. We hypothesize that the provision of the *"WE CALL" *intervention over the first six months post-stroke, compared to the *"YOU CALL" *will have three positive effects persisting 6 months beyond the intervention period:

1) A decreased unplanned-used of health services for negative events;

2) An improved quality of life;

3) Less depressive symptoms, a better participation in daily activities and social roles, and an increase in planned health visits for promotion and secondary stroke prevention;

In addition, we hypothesize that:

4) Participants with higher comorbidity level will benefit more from the active intervention given the increased complexity of their health status and,

5) Participants with access to secondary stroke prevention (SPC) clinic will benefit more from the intervention than those without SPC access.

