Additional written information will be provided when and as needed. Participants will be referred to local community services as necessary and/or directed to their family doctors when they experience health problems (including depression). Written information on secondary stroke prevention and effectiveness of rehabilitation interventions post-stroke will be made available either directly via an Internet website - StrokEngine - or through CD's or paper copies, for those who do not have easy access to the Internet or a computer.

**YOU CALL **group participants are provided with the name and phone number of a THCP who is not involved in providing the "we call" intervention, whom they are free to contact should they feel the need to. This THCP is different from the ones providing the intervention to the "we call" group to minimize potential contamination between the interventions due to THCPs. THCP-you call is instructed to provide only information on topics initiated by the participant. He/she is instructed to provide complete information to adequately answer participants' requests but does not probe on other issues. The use of this intervention as a control, which is very ecological (most individuals are provided with stroke information pamphlets and phone numbers to contact), is more acceptable ethically than a "pure" control group receiving no intervention (or only usual care) and provides some control for the Hawthorne effect.

For both groups, frequency and content of each call is documented. Also, for both groups, intervention takes place in the first six months following baseline measures. This time frame was chosen given it takes that long for individuals with stroke to cope and adapt to their new reality [38] as well as to resume daily activities and social roles such as driving and leisure [16].

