### Sample size

Because the FITT study in the US was still underway at the time of writing this protocol, sufficient data on the unplanned-use of the health care system was not available. However, considering the high prevalence of stroke recurrence, emergency visits because of medications errors, falls and depression in the stroke population, we estimated a mean number of unplanned-use equal to three in the first six months post-stroke with a standard deviation of one unplanned-use. If we aim to decrease unplanned-use of the health care system by 10%, a sample size of 175 participants in each group is necessary with an alpha level set at 5% (for a bilateral test) and a power of 80%. A sample size of 57 individuals per group would be required to detect a two-point difference in the Quality of Life Index global score using data from a previous study [67] on quality of life of individuals with stroke (n = 72; mean = 20.91 ± 3.8). Given these estimates and considering a potential loss to follow up of 10%, a total sample of **384 individuals **is targeted for recruitment. These numbers are sufficiently large (using same parameters, required n < 65/group for participation and depression) to allow for large effect size of secondary outcomes and to do subgroup analysis according to comorbidity level.

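### The calendar coding rule has no correct code for a booked visit for a negative event or an unscheduled preventive visit, so either visit count can be contaminated and rescheduled events cannot be told from fewer events

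*Protocol article*

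**What the plan says.** All of the outcome text is in item 1 of the protocol article's section Detailed description of outcome measures.

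- The calendar captures the reason for each contact: "reasons (e.g. a fall, dizziness, stroke, follow up appointment, physical therapy, etc".
- It also captures "most importantly if the visit was planned (scheduled) or not (emergency").
- Three stroke specialists outside the study screen the entries "to differentiate noise (such as emergency for a cold or planned-visits for foot care) versus any stroke-related use of the health care system".
- The coding rule follows: "Each entry is being dichotomised as either planned for health promotion/prevention or unplanned for a negative event".

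Unplanned use for negative events is one of two primary outcomes. Planned use for promotion and prevention is a secondary outcome, and the section The research objective counts "an increase in planned health visits for promotion and secondary stroke prevention" as a benefit of WE CALL.

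The section Interventions describes the two arms. WE CALL staff phone weekly for two months and less often after that. They ask about six areas each time, among them depression and physical health. Participants are "directed to their family doctors when they experience health problems (including depression"). In the other arm, "THCP-you call is instructed to provide only information on topics initiated by the participant", without probing further.

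**The concern.** Scheduling and reason are separate attributes, and the rule treats them as one. It works only if every stroke-related scheduled contact is preventive and every stroke-related unscheduled contact is for a negative event. The outcome also covers psychologists, social workers and therapists, whose appointments are plausibly booked and often for a problem, so the two unnamed combinations are unlikely to be empty.

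The screening step does not help. It removes contacts unrelated to stroke, and a booked appointment for dizziness or low mood is related.

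Two things are at stake. First, entries that fit neither label must be mislabelled or dropped, and the arms may differ in how many they generate, because one arm is actively asked about problems and pointed to a doctor. Second, the trial could report fewer unplanned visits and more planned ones with no way to tell whether participants had fewer negative events or the same events seen by appointment.

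**Working it through.** **1. The four combinations.**

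| | Negative event | Prevention or follow-up |
|---|---|---|
| Unscheduled | named by the rule; mean *u* per person | not named; mean *w* |
| Scheduled | not named; mean *b* | named by the rule; mean *p* |

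An example for *b* is a booked appointment after a fall. An example for *w* is a walk-in blood-pressure check.

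**2. What coders can do with *b* and *w*.** The article does not say, so each route is followed through.

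| Route | Primary count | Planned-prevention count |
|---|---|---|
| Both axes coded (reference) | *u* | *p* |
| A. Follow scheduling | *u* + *w* | *p* + *b* |
| B. Follow reason | *u* + *b* | *p* + *w* |
| C. Drop entries that fit neither label | *u* | *p* |

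Write Δ for WE CALL minus YOU CALL. Route A shifts the secondary comparison by Δ*b* and the primary by Δ*w*. Route B shifts the primary by Δ*b* and the secondary by Δ*w*. Route C shifts neither, but *b* and *w* vanish from the coded data. All negative-event contacts, *u* + *b*, cannot be obtained from the coded counts under A or C. Under B they replace the defined primary, and *u* alone is lost.

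**3. Could Δ*b* or Δ*w* differ from zero?** Probing and direction to a family doctor occur in WE CALL only, which makes a positive Δ*b* plausible. Encouragement of prevention could also raise *w*, and under route A that counts against WE CALL. No rates are given, and the article does not say whether a visit prompted by a caller is booked or walk-in. Size and net direction are therefore open.

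**4. Illustration on the plan's own scale.** The section Sample size says: "we estimated a mean number of unplanned-use equal to three in the first six months post-stroke with a standard deviation of one unplanned-use". A 10% reduction is 0.10 × 3 = 0.3 visits. Reproducing the plan's figure: n per group = 2 × (1.960 + 0.842)² × 1² / 0.3² = 174.4, rounded up to 175, which agrees with the article.

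Assume that a share *s* of 3 negative-event contacts moves from emergency to booked in WE CALL only, with *w* = 0, *p* equal in both arms and total negative-event contacts equal. *s* is an assumption. The entries are between-arm differences.

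| *s* | Primary: both axes, A or C | Primary: B | Secondary: both axes, B or C | Secondary: A | All negative-event contacts |
|---|---|---|---|---|---|
| 2% | −0.06 | 0 | 0 | +0.06 | 0 |
| 5% | −0.15 | 0 | 0 | +0.15 | 0 |
| 10% | −0.30 | 0 | 0 | +0.30 | 0 |

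With 175 per group and SD 1, the standard error is √(2/175) = 0.107. The chance of a significant primary result in the second column is 8.7%, 28.9% and 80.1% for the three rows. It is the same under correct two-axis coding as under A or C, so these probabilities say nothing about miscoding. The coding error is the spurious gain in the *Secondary: A* column, or under B the loss of a real change in the primary. Only two-axis coding yields the primary, the secondary and the last column together.

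**The case against.** A reader might infer that the rule manufactures a primary effect: one in ten contacts rescheduled in WE CALL gives 0.3 visits, the whole design effect. The documents do not support that. The primary is defined as unplanned use for negative events, and a booked visit lies outside it under the correct coding too. The second column of the illustration is the same before and after the repair. Moving emergencies into booked care is also within the trial's aims, since its hypotheses include both fewer unplanned and more planned visits.

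A reader might also infer that booked problem visits are in fact coded as prevention, or that the bias must favour WE CALL. The article states neither. YOU CALL participants can also phone a trained professional, and caller-prompted emergency visits would count against WE CALL.

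It can further be said that three specialists scrutinise each entry, that borderline rules may sit in a coding manual not shown, that the cost-utility analysis counts related use under either label, and that quality of life, the other primary, does not depend on visit labels. These points limit the stakes. They do not remove the problem, because the article states a rule for every entry and describes it as already in use. Applied as written, it leaves even a careful coder no correct label for the two unnamed combinations.

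**Conclusion.** The point holds as a defect in a stated coding rule. It does not show that the primary outcome is miscoded in WE CALL's favour. Stroke-related entries in two of the four combinations must be mislabelled or dropped. Depending on how coders resolve them, the planned-prevention secondary outcome absorbs problem visits, or the primary absorbs scheduled ones; unscheduled preventive visits raise the mirror-image difficulty.

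The between-arm error is one-for-one with Δ*b* or Δ*w*. That these differ by arm is an inference from the intervention descriptions, and their size and net sign cannot be derived from the documents.

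Separately, a real shift from emergency to booked care counts properly as a change in the primary, but the coded counts cannot show whether negative events became fewer or were rescheduled. This bears on how a primary result is read and on the validity of one secondary outcome. It should be repaired before the visit data are analysed.

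**What to change.** Code every entry that passes the noise screen on two separate variables: scheduled (yes or no), and reason (negative event, or prevention and follow-up). Then:

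- keep the primary as unscheduled and negative event;
- keep the planned-use secondary as scheduled and prevention;
- report all four cells by arm;
- add a supportive analysis of all negative-event contacts regardless of scheduling, labelled as supportive so that it does not replace the primary.

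The calendar already holds both attributes, so no new data are needed and the sample size does not change. The cost is a revised coding sheet for the same three coders and a short re-code of entries already processed.
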